## 5.4 Management of adverse events and new findings

### 5.4.1 Definitions

**Adverse event** (article R1123-46 of the Public Health Code)

Any toxic signs occurring to a person, who is participating in research involving the human body, whether these signs are linked to the research or not or to that product, which is the subject of such research.

**Adverse reaction** (article R1123-46 of the Public Health Code)

Adverse reaction occurring to a person who is participating in research involving the human body, whether this reaction is linked to the research or not or to that product, which is the subject of such research.

**Adverse reaction of an experimental drug** (article R1123-46 of the Public Health Code)

Any toxic and adverse reaction to an experimental drug, whatever may be the dose administered.

**Serious adverse event or serious adverse reaction** (article R1123-46 of the Public Health Code and ICH guide E2B)

Any adverse event or reaction which:

- causes death,
- puts the life in danger of the person submitting to research,
- requires hospitalisation or prolongs that hospitalisation,
- causes a severe or lasting incapacity or handicap,
- leads to a congenital anomaly or malformation,
- or any event deemed to be medically serious,

and pertaining to the drug, whatever may be the dose.

The expression “puts the life in danger” is reserved for an immediate life threatening event, at the time of the adverse event.

**Unexpected adverse reaction** (article R1123-46 of the Public Health Code)

- For research pertaining to a drug: any adverse reaction to the product of a nature, severity, frequency or change not conforming with the benchmark safety information specified in the summary of product characteristics.

**New finding** (article R1123-46 of the Public Health Code)

- Any new data likely to lead to a re-evaluation in respect of the benefits and the risk of the research or of the product, which is the subject of the research, to modifications in the use of this product, in the conduct of the research, or documents relating to the research, or the suspension or the interruption or the change in protocol of the research or of similar research.
- For trials pertaining to the initial administration or use of the health product for people presenting no illness: any serious adverse reaction.

#### 5.4.2 Description of expected adverse events

Expected adverse events for the trial's drugs are those specified in the Summary of Product Characteristics (SPC) for Plaquenil®, Imatinib TEVA®, Avigan® and Micardis®.

The Summary of Product Characteristics (available online on the trial eTMF) provides the complete list and the level of risk for each drug. The risks of adverse reactions for the 4 experimental drugs for short treatments of 10 days are slim. Adverse reactions, whether the most frequent (even if they are benign) or the most serious (even if they are rare) are as follows:

- Hydroxychloroquine: abdominal pain, diarrhoea, nausea, vomiting, lengthening of the QT interval and *torsades de pointes* or ventricular tachycardia, hypersensitivity, medullar aplasia, pruritus, rash, headache and hypoglycaemia.
- Telmisartan: rash, orthostatic hypotension, cardiac decompensation, hypersensitivity and elevation of transaminases.
- Imatinib: cardiac decompensation, elevation of transaminases, neutropenia, thrombocytopenia, anaemia, pancytopenia, headache, dyspnoea, cough, abdominal pain, vomiting, nausea, diarrhoea, cramps and water retention.
- Favipiravir: elevation of transaminases, diarrhoea, nausea, vomiting, headache, hyperuricemia and hypertriglyceridemia.

Any adverse event, neither appearing in the list of expected events, nor in the latest version of the benchmark document, is deemed to be unexpected.

#### 5.4.3 Conduct to be maintained by the researcher in the case of adverse event or new finding

##### 5.4.3.1 Reporting of adverse events (AE)

The researcher is responsible for reporting adverse events occurring between the date of signature of consent and the end of the participant's participation, apart from those detected before the first application of the trial's treatment. If the clinical or biological adverse event is present at the time of signature of consent, only its deterioration needs to be recorded.

In the context of this protocol, all adverse events must be reported.

The researcher is to record adverse events (clinical and biological) in the observations log. Such adverse events are researched upon every visit over the course of the study by the posing of questions and during the participant's clinical examination.

#### 5.4.3.2 Immediate notification of serious adverse events (SAEs) and new findings

The researcher is to evaluate each adverse event with regard to its seriousness.

The researcher must notify the Safety and Monitoring Unit by fax, email or via the eCRF [SDPM], **immediately** from the day of becoming aware of it, of all SAEs and all new findings, with the exception of the following SAEs:

- Pre-existing or documented pathology before the signature of consent to the trial and remaining at a degree of severity equal or lesser than that preceding the initial treatment of the trial.
- Hospitalisation for medical or surgical treatment scheduled before the research;

If the researcher becomes aware of a Serious Adverse Event, for which he suspects a causal link with the research, occurring after the end of research for any participant whom he has treated, he is to inform the Safety and Monitoring Unit immediately.

**The researcher must document the event to the best of his ability, providing, if possible, the medical diagnosis.** The researcher must satisfy himself that information relevant to the follow-up has been communicated to the Safety and Monitoring Unit as soon as possible.

The researcher must send on, in addition to the form for notifying SAEs, copies of the laboratory results or examination or hospitalisation reports, giving details of the Serious Adverse Event, including the relevant negative results **without omitting to anonymise these documents** and include the participant's number and code before sending.

**The researcher must monitor the participant having presented with an SAE until its resolution, stabilisation at a level judged by him as medically acceptable or the previous state resuming, even if the participant has stopped the research's procedure.** Any addition to the information pertaining the changes in the event, if it has not been mentioned in the first report, shall be sent to the Safety and Monitoring Unit by the researcher.

All Serious Adverse Events, for which the researcher or the Safety and Monitoring Unit deems that a causal relationship could plausibly be foreseen, are to be considered as suspicions of Serious Adverse Reactions.

#### 5.4.3.3 Recapitulating table of the flow of notifications per event type

| EVENT TYPE                       | NOTIFICATION METHODS                                                                                                             | NOTIFICATION SCHEDULE TO THE SAFETY AND MONITORING UNIT |
|----------------------------------|----------------------------------------------------------------------------------------------------------------------------------|---------------------------------------------------------|
| Non-serious adverse event | AE form in the observations log                                                                                                  | No immediate notification                               |
| Serious adverse event     | “AE” form in the observations log and initial SAE declaration form (+ Follow up, if necessary)
+ written report, if necessary | Immediate notification                           |
| New finding                      | Form for sending out an alert (EN-RCL-515) and form “AE” from the observations log, if applicable                                | Immediate notification                           |

#### 5.4.4 Declaration by the sponsor of Suspected Unexpected Serious Adverse Reactions and new findings.

The Safety and Monitoring Unit is to evaluate if the Serious Adverse Reaction is expected or unexpected, while using the benchmark document as its basis (SPCs of the trial's drugs).

The Safety and Monitoring Unit is to declare to the relevant authorities any Suspected Unexpected Serious Adverse Reaction (SUSAR) occurring in France and outside the national territory and within the following timescales:

- 1). In the case of the SUSAR having caused death or threatened life, immediately from the day of the sponsor becoming aware of it,

- 2). In the case of other SUSAR, at the latest within a timescale of 15 days from the day of the sponsor becoming aware of it.

The Safety and Monitoring Unit is to declare in the form of a follow-up report to the ANSM that relevant additional information regarding the SUSARs:

- In the case of suspicion of SUSAR, having brought about death or threatened life, such information is to be notified within a timescale of 8 days from the time of the declaration mentioned in point 1)
- In other cases of SUSAR and for new findings, relevant additional information is to be sent within a new timescale of 8 days from the timescale mentioned in point 2).

Pertaining to any drug study, the Safety and Monitoring Unit is to record on the EudraVigilance database all SUSARs.

The Safety and Monitoring Unit is to declare immediately any new findings occurring over the course of the research:

- to ANSM,
- to the Institutional Review Board.

The sponsor and the researcher are to take the appropriate urgent measures. The sponsor shall inform the relevant authority and the Institutional Review Board of such.

#### 5.4.5 Annual safety report

On the anniversary date of the research's authorisation, the Safety and Monitoring Unit shall draw up a safety report comprising:

- the list of Serious Adverse Reactions likely to be linked to experimental treatments of the research, including the expected and unexpected Serious Adverse Reactions, occurring in the relevant trial over the period covered by the report,
- a concise and critical analysis of the safety of participants taking part in the research.
- the summary table of all Serious Adverse reactions occurring during the relevant trial since the start of the research.

This report is to be sent to ANSM and the IRB within 60 days after the anniversary date of the research's authorisation.

#### 5.5 Safety of staff

Given the risk of transmission of SARS-CoV2, this study raises questions of safety. The researchers shall give particular attention to the following points:

- Research staff taking part in the study shall be informed of the nature of the research, including the personal risks and the need to follow strict prevention procedures [SDPM].
- Research and care staff taking part in the study shall be trained in standard international procedures for the prevention of SARS-CoV2 transmission and shall be supplied with international standard equipment before coming into contact with the patients. The non availability of adequate equipment shall lead to a revision of the procedures.
- The participants in the trial and their relatives shall receive an explanation of those precautions to be taken to prevent transmission.

## 6 Statistical analysis

- Inclusion and exclusion from statistical analysis

Participants who died, were lost to follow-up or withdrew consent will be included in the analysis. Participants with at least one of the following conditions could be excluded:

- Having never taken trial treatment or ignoring the allocated arm
- Included without signing a consent form
- Included despite non-compliance with at least one major eligibility criterion
- Having withdrawn consent

The SAB will review cases documentation collected by the trial team and will take an exclusion decision blinded of the randomisation arm and the participant's post inclusion evolution.

Major deviations from eligibility criteria are defined as any deviation on the following criteria:

- Positive SARS-CoV-2 RT-PCR
- Age  $\geq$  65 years

Randomisation treatment discontinuation will be managed as follows:

- On intention to treat (ITT)  
Any participant will be analysed in the allocated arm, disregarding eligibility deviations or non-compliance with randomisation treatment.  
All data will be used.
- On treatment (OT)  
Any participant will be analysed in the allocated arm, irrespective of eligibility deviations or non-compliance with randomisation treatment.  
All data observed after discontinuation of randomisation treatment will be dropped.
- Per protocol (PP)  
Any participant will be analysed in the allocated arm, irrespective of minor eligibility deviations or minor non-compliance with randomisation treatment.  
All data from any participant with a major eligibility deviation or a major non-conformity with randomisation treatment will be dropped.
- As treated (AT)  
Any participant will be analysed with respect to the actually received treatment, irrespective of the allocated treatment.

Missing values will be managed as follows:

- Analysis on available data (AD): any missing value will be ignored.
- Missing as failure (M=F) procedure: any missing value will be analysed as a failure (main endpoint: disease worsening)
- Worst case procedure (WC):  
First sub-analysis: Any missing data is analysed as a success in the first arm, and as a failure in the second arm.  
Second sub-analysis: Any missing data is analysed as a failure in the first arm, and as a success in the second arm  
The conclusion will be that of each sub-analysis if they are identical.
- Inverse probability weight (ITW) procedure:  
Weighting of values by estimated probability that a value is missing, obtained through modelling from baseline participants' characteristics and follow-up characteristics collected for all participants.

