## **8 Monitoring**

### **8.1 Scientific Advisory Board**

- The Scientific Advisory Board (SAB) is to meet by teleconference every other week.
- It is to be composed of:
  - The coordinating investigator and the research coordinator, the senior methodologist, the senior statistician, the project manager and the monitoring advisor.
  - 3 experts in the areas of infectious diseases, clinical trial and immunological methods and the pharmacological monitoring of clinical trials.
  - One representative for the sponsor and for each partner institution.
- This guarantees that the trial is held in an appropriate manner at the scientific, clinical and ethical levels. That includes:
  - Checking that the team charged with the trial is observing protocol and ensuring the safety of participants
  - Guaranteeing the relevance of the trial's questions and the validity of its methods.
  - Making decisions regarding those necessary and relevant changes to the protocol.
  - Deciding whether to open or close trial sites.
  - Checking observance of the rules regarding access to data, reports and trial publications.
  - Ensuring liaison with the DSMB and the regulatory authorities.

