### 9.3.3 Data security

Access to the private site for randomisation is secured, controlled and traced; authentication is reserved for team members and the administration of the user accounts assured by the project's IT team. Access to the complete randomisation list is exclusively reserved for the project's statisticians.

All information on participants shall be strictly confidential. Information, such as the participant's name or any other data able to lead to identification of the participant, shall not be recorded in the trial's database.

All paper documents and digital forms necessary for data management are reserved for authorised trial staff.

The trials' database shall only be accessible by means of personal user name and password. Management of access rights to the software is the responsibility of the REDCap administrator at the CHU de Bordeaux. A list of authorised users of the database shall be updated during the study.

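### Section 6 both includes and allows exclusion of participants who withdrew consent, and its case-by-case exclusion list contradicts the intention-to-treat primary analysis

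*Protocol*

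**What the plan says.** Section 6 opens with a rule for who enters the statistical analysis: "Participants who died, were lost to follow-up or withdrew consent will be included in the analysis". The next sentence reads "Participants with at least one of the following conditions could be excluded", and its list contains "Having never taken trial treatment or ignoring the allocated arm", inclusion without a signed consent form, failure of a major eligibility criterion (positive RT-PCR, or age 65 and over), and "Having withdrawn consent". No analysis set is named.

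On who decides, section 6 says "The SAB will review cases documentation collected by the trial team and will take an exclusion decision blinded of the randomisation arm" and adds that the decision is also blind to the participant's course after inclusion.

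The ITT definition in the same section is "Any participant will be analysed in the allocated arm, disregarding eligibility deviations or non-compliance with randomisation treatment", with all data used. Section 6.1 then makes ITT with missing counted as failure the analysis for each primary-endpoint test, interim analyses included.

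Section 8.1 gives the SAB's membership, which includes "The coordinating investigator and the research coordinator, the senior methodologist, the senior statistician, the project manager and the monitoring advisor". The summary and section 1.4 describe the trial as open-label.

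**The concern.** Two rules for the same people cannot both be applied. A withdrawn participant is either in the primary analysis, where an unobserved outcome counts as a failure, or absent from it. A never-treated participant is either analysed in the allocated arm, as the ITT definition requires, or removable.

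Never starting treatment and withdrawing consent both arise after randomisation. In an open-label trial with a vitamin control they can depend on the arm, so removing such people can undo the balance that randomisation gave. The word *could* makes each removal a matter of discretion. At stake is whether the result called ITT is an analysis of everyone randomised, and whether that is settled before outcomes are known.

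**Working it through.** **1. The texts side by side**

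| Group | Opening rule or list, section 6 | ITT definition (section 6), applied by section 6.1 |
|---|---|---|
| Withdrew consent | Included, then excludable | In the allocated arm; missing outcome = failure |
| Never took treatment | Excludable | In the allocated arm; non-compliance disregarded |
| Major eligibility deviation | Excludable | In the allocated arm; eligibility deviations disregarded |

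The list stands before any set is defined. The per-protocol definition carries its own rule for major deviations, and section 6.3.7 defines the safety set separately. Nothing confines the list to a set other than ITT.

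**2. The design figure**

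Inputs from section 6.2.1: 25% against 12.5%, power 80%, one-sided tests, futility alphas 0.65, 0.45 and 0.25 at 30, 60 and 102 per arm, and 169 per arm at the end. The efficacy alpha is given only as O'Brien-Fleming, so I assume one-sided 0.025 and show 0.05 as the range.

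- Two-proportion formula at 0.025: 152 per arm, or 168 with continuity correction, against the stated 169.
- Four stages, with the final test at 0.025: joint power 79.5%, against the stated 80% (84.5% at 0.05).

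The stated size is reproduced and is not in dispute.

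**3. Dropping never-treated participants, no true effect (rates assumed)**

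Both arms have 25% risk when everyone is counted. A fraction e of the experimental arm, with event risk q, is dropped; nobody is dropped from control.

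- Remaining experimental risk = (0.25 − e·q)/(1 − e). With e = 0.05 and q = 0.50: (0.25 − 0.025)/0.95 = 0.2368, on 169 × 0.95 = 160.55 participants.
- Pooled risk 0.2436; standard error 0.04731 (null) and 0.04728 (unpooled).
- Error = Φ[(0.25 − 0.2368 − 1.960 × 0.04731)/0.04728] = Φ(−1.68) = 0.046, against a nominal 0.025.

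| e | q | Error, nominal 0.025 | Error, nominal 0.05 |
|---|---|---|---|
| 5% | 25% | 0.025 | 0.050 |
| 5% | 50% | 0.046 | 0.086 |
| 10% | 50% | 0.084 | 0.144 |

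If those dropped have the same risk as the rest, nothing is inflated.

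**4. Withdrawn participants, true halving (rates assumed)**

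A fraction w withdraws in each arm with the outcome unobserved. Fixed-sample test, 169 per arm; power with none withdrawn is 84.1% at 0.025.

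- Counted as failures, w = 0.05: control 0.95 × 0.25 + 0.05 = 0.2875; experimental 0.95 × 0.125 + 0.05 = 0.16875. Power = Φ[(0.11875 − 1.960 × 0.04565)/0.04519] = Φ(0.65) = 74.1%.
- Excluded, w = 0.05: 25% against 12.5% on 160.55 per arm. Power = Φ[(0.125 − 1.960 × 0.04356)/0.04300] = Φ(0.92) = 82.2%.

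| w | One-sided alpha | Counted as failures | Excluded |
|---|---|---|---|
| 5% | 0.025 | 74.1% | 82.2% |
| 5% | 0.05 | 83.3% | 89.3% |
| 10% | 0.025 | 64.6% | 80.1% |
| 10% | 0.05 | 75.6% | 87.8% |

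With the futility stages included, the 5% pair at 0.025 becomes about 69% and 78%.

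**5. The blind**

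Never starting treatment and withdrawing are themselves events after inclusion, so a board judging them is not blind to that course. Section 9.5 sends each SAB meeting a list of withdrawals and interruptions. Section 9.3.3 says "Access to the complete randomisation list is exclusively reserved for" the project's statisticians. That the SAB's senior statistician is one of them is likely, but not stated. The protocol describes no way of keeping the blind.

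**The case against.** The specific rules may be said to govern: ITT is defined without exclusions, section 6.1 fixes it for the primary endpoint, and a permissive list can be read as serving the per-protocol set. That is a sensible guess at the intent. The text does not say so, and the per-protocol set already has its own rule.

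A reader might infer that an unblinded board picks the primary population. The documents do not support that. The decision is stated to be blind; masked dossiers are possible in an open-label trial; and the section 9.5 list is not said to be by arm. Doubt is justified, impossibility is not.

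The phrase about ignoring the allocated arm is ambiguous. The English appears to be translated from French, and it may mean being unaware of the arm instead of departing from it. The point does not need either reading.

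A reader might also infer that leaving the choice open inflates false positives on its own. With no drug effect, if 8% of control and 4% of experimental participants withdrew and all counted as failures, the rates would be 31% (0.92 × 0.25 + 0.08) against 28% (0.96 × 0.25 + 0.04). The four-stage false-positive rate would be about 12 to 13% at one-sided 0.05, or about 8% at 0.025. That inflation comes from counting missing as failure under unequal withdrawal, and exclusion would remove it. At 0.05, equal withdrawal of 6% gives about 4%, and the reversed split about 1%. The example therefore does not argue for keeping these participants. It does identify a real cost of doing so.

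**Conclusion.** The contradiction stands on the wording of section 6. Withdrawn participants are both included and excludable. Never-treated participants and those with major eligibility deviations are excludable at discretion from an analysis that sections 6 and 6.1 define as ITT. A later analysis plan could follow either rule and still claim to follow the protocol.

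The result can move in either direction: error up from 0.025 to about 0.046 in one illustration, and power of about 74% or 82% in the other. The withdrawal and non-treatment rates, the risk of those dropped and the efficacy alpha are all assumed. The illustrations show that the choice matters, not how large the effect will be in this trial. The stated blind of the SAB decision is doubtful and should not carry the weight of the rule. The wording should be corrected before the first interim analysis.

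**What to change.** - Define the primary ITT set as every randomised participant with a signed consent, analysed in the allocated arm.
- State one rule for withdrawn consent: the participant stays in ITT, data up to withdrawal are used, and an outcome not observed by then is missing.
- Delete three grounds for exclusion from ITT: never treated or ignoring the allocated arm, withdrawn consent, and major eligibility deviation.
- Use non-treatment and major eligibility deviation only to define the per-protocol set, by a fixed rule in place of case review by the SAB.

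The change is to wording; 169 per arm stays. There are three costs. Never-treated participants dilute the effect slightly. Counting withdrawn participants as failures gives lower power than excluding them (section 4 of the working). And unequal withdrawal between arms can bias the comparison when missing counts as failure. The primary result should therefore be read beside the worst-case and inverse-probability-weighted analyses already planned in section 6.3.4.

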## 6.2 Sample Size

### 6.2.1 Participants not taking ACEI or ARB before inclusion

The incidence assumptions on primary endpoint are based on extrapolations from aggregated data published in other contexts thus far. The DSMB will check these assumptions and recommend a sample size revision, if needed.

We assumed that the proportion of participants reaching the primary endpoint at D14 in the control arm could be up to 25%. An experimental treatment will be deemed efficient if this proportion is reduced by at least one half. We also considered a power of 80% for all tests.

Three futility (interim) analyses will be performed successively. We defined successive arm discontinuation thresholds for the one-way first type error alpha using STATA package NStageBin for conception and sample size of MAMS trials (65,66).

Two efficacy analyses (interim n°3 and primary) will be performed successively. We will use the O'Brien & Fleming procedure to define the first type error alpha for each analysis, based on the data observed at the first futility analyses (67,68).

Sensitivity analysis at D28 will be exploratory only, without impact on sample size.

Tests of difference between arms will be one-sided. Arm discontinuation thresholds and sample size for each analysis are given here below:

| Analysis    | Trigger
Number of participants in the control arm having reached D14 | Objectives     | Alpha           |
|-------------|-------------------------------------------------------------------------|----------------|-----------------|
| Interim n°1 | 30                                                                      | Futility       | 0,65            |
| Interim n°2 | 60                                                                      | Futility       | 0,45            |
| Interim n°3 | 102                                                                     | Futility       | 0,25            |
|             |                                                                         | Early efficacy | O'Brien-Fleming |
| Primary     | 169                                                                     | Efficacy       | O'Brien-Fleming |
| Sensitivity | End of trial                                                            | Efficacy       | 0,05            |

The sample size required is 169 participants by arm (845 overall). Since the "Missing as failure" procedure is used, there is no need to increase sample size to account for missing data.

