### 6.3.4 Primary outcome for participants not taking ACEI or ARB before inclusion

The primary endpoint will be described at each visit and phone interview, as a binary outcome and a time-to-event outcome.

The primary analysis is the set of interim and final analyses on the primary endpoint at D14 (futility and efficacy).

Secondary analyses of the primary endpoint will explore variants of the primary analysis, concerning:

- Management of randomisation treatment discontinuation: on treatment, per protocol, as treated
- Management of missing values: worst case, inverse probability weighting
- Primary endpoint at D7

The sensitivity analysis will repeat the primary analysis at D28 to confirm the results of D14.

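### The worst-case check on missing outcomes concludes only when its two opposite extremes agree, has no stated reading when they differ, and at modest missingness they often will

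*Protocol*

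**What the plan says.** Section 6 of the protocol defines four ways to handle missing outcomes: available data, missing as failure, worst case, and inverse probability weighting. Section 6.1 makes intention to treat with missing as failure the method for every analysis of the primary endpoint.

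The worst-case procedure has two sub-analyses. In one, every missing outcome is a success in the first arm and a failure in the second. In the other, the scoring is reversed. The rule for reading them is: "The conclusion will be that of each sub-analysis if they are identical". Nothing is said about the case where they are not identical.

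Section 6.3.4 lists the secondary, missing-data variants of the primary analysis: "Management of missing values: worst case, inverse probability weighting". Weighting is described in section 6 as a model of the probability of being missing, built from baseline and follow-up characteristics. Section 6.2.1 uses missing as failure as the reason for adding no participants for missing data, and states no expected missing rate.

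**The concern.** The two extremes answer different questions. For a superiority claim, the extreme that favours the drug is nearly always passed when the drug works. The real test is the other one, where missing controls count as successes and missing treated participants as failures. Requiring agreement therefore amounts, for efficacy, to passing that unfavourable extreme. When it fails, the procedure has no stated conclusion.

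This matters because the primary scoring is a strong assumption in an open-label trial followed at home and by telephone, where loss could differ between arms. Scoring missing as failure adds events to whichever arm loses more people, so it can move the estimate either way. A reader of a positive result will ask how far it depends on that scoring. Weighting on recorded characteristics cannot answer this if missingness depends on the unseen outcome. Worst case can, but its rule gives all or nothing.

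**Working it through.** **Inputs from section 6.2.1.** Control proportion 25%. "An experimental treatment will be deemed efficient if this proportion is reduced by at least one half", so 12.5% in the experimental arm. "We also considered a power of 80% for all tests". "Tests of difference between arms will be one-sided". 169 per arm. For the final efficacy level, "We will use the O'Brien & Fleming procedure to define the first type error alpha for each analysis"; no overall level is given in the primary row of the table (0.05 appears only in the D28 sensitivity row). Both one-sided 0.05 and 0.025 were therefore run.

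**Assumptions.** Missing rate 1% to 10%, equal in both arms and unrelated to outcome. A sub-analysis concludes by being significant or not. Interim looks are left out of the simulation.

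**1. Reproducing 169.** With difference d = 0.125 and mean proportion 0.1875, the power of a look at n per arm is

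Φ[(d√n − z_α √(2 × 0.1875 × 0.8125)) / √(0.25 × 0.75 + 0.125 × 0.875)].

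- Final look at 169, α = 0.025: (0.125 × 13 − 1.96 × 0.552) / 0.545 ≈ 1.00, giving 84.1%.
- Final look at 169, α = 0.05: 90.6%.
- Futility looks at 30, 60 and 102 with α 0.65, 0.45 and 0.25: 95.0%, 95.1% and 94.9%.
- All four looks jointly (multivariate normal): 79.5% at final one-sided 0.025, and 84.5% at 0.05.

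So 169 with 80% power reproduces at one-sided 0.025.

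**2. Worked case, 8 missing per arm (about 5%).** Observed 161 per arm, with expected events 0.25 × 161 = 40.25 and 0.125 × 161 = 20.125. The test is pooled, Z = (p₁ − p₂) / √(2p̄(1 − p̄)/169).

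- Missing as failure: 48.25/169 = 28.6% against 28.125/169 = 16.6%, Z = 2.62.
- Extreme favouring the drug: 48.25/169 = 28.6% against 20.125/169 = 11.9%, Z = 3.81.
- Extreme against the drug: 40.25/169 = 23.8% against 28.125/169 = 16.6%, Z = 1.64, one-sided p = 0.0503.

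With exactly the planned effect and 8 missing per arm, the unfavourable extreme sits on the 0.05 boundary, so passing it is close to a coin toss.

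**3. Simulation, 400,000 trials per setting, 169 per arm.**

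| Missing | Extremes disagree, α 0.05 | Extremes disagree, α 0.025 | Disagree given positive missing-as-failure, α 0.05 | Same, α 0.025 |
|---|---|---|---|---|
| 1% | 8.5% | 12.1% | 4.8% | 7.2% |
| 2% | 18.0% | 25.0% | 11.8% | 16.7% |
| 5% | 51.7% | 62.5% | 43.4% | 53.0% |
| 10% | 91.3% | 95.1% | 88.6% | 92.8% |

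Repeat runs at 5% and α 0.05 give 51% to 52%. Fixing exactly 8 missing per arm gives 48.9%. At an O'Brien-Fleming-type final level of 0.0465 the figure is 52.9%.

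**4. Where the disagreement comes from.** At 5% missing and α 0.05, the favourable extreme is significant in 99.0% of trials, the unfavourable one in 47.2%, and both in 47.2%. So agreement on efficacy is the unfavourable extreme alone.

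**5. What a graded check would add.** Take the same setting and a moderate adverse scenario: 25% events among missing controls and 50% among missing treated participants. About 94% of positive missing-as-failure results stay significant, against 57% confirmed by the worst-case rule. The agreement rule cannot show that difference.

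**The case against.** Several points on the other side are sound.

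- A reader might infer that a worst-case disagreement leaves the missing-as-failure result untested. It does not. Section 6.3.4 plans inverse probability weighting beside worst case, and both extremes are computed and can be reported whatever they show.
- Nor is the check silent. A disagreement shows that the answer depends on the unobserved outcomes at the extremes, which is what a bounding analysis is for. The protocol just does not say it will be read that way.
- Worst case is secondary, so a disagreement changes no trial decision.
- Reading the unfavourable extreme alone would confirm efficacy exactly as often as the agreement rule (47.2% in step 4). Relabelling gains nothing; only a graded analysis does.
- The missing rate is assumed, and the result depends heavily on it. The design works against missing D14 outcomes: contacts are scheduled on Days 1, 3, 5, 7, 9, 12 and 14, and section 5.3.5 sends the mobile team when a remote contact fails. At 1% to 2% missing, the extremes usually agree.
- The simulation uses equal random missingness, so it does not measure the effect of loss that differs by arm.
- Section 6.3.1 leaves details of secondary analyses to a statistical analysis plan, which was not available here.

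The last point does not dispose of the matter. The decision rule is written in the protocol itself and covers only one of its two possible outcomes.

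**Conclusion.** The point holds as a gap in a secondary analysis. The worst-case rule concludes only on agreement and fixes no reading otherwise. Under the design assumptions, the unread outcome ranges from uncommon at 1% missing (9% of trials at one-sided 0.05, 12% at 0.025) through about half or more at 5% (52% and 63%) to nearly certain at 10% (91% and 95%). For a positive missing-as-failure result at one-sided 0.05, the corresponding figures are 5%, 43% and 89%. They rest on an assumed missing rate, equal random missingness, the full planned effect and no interim looks.

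The protocol does not support the stronger conclusion that the trial could say nothing about robustness: weighting is planned, and discordant extremes are themselves informative. What remains is that the only planned check on outcome-dependent missingness is all or nothing. The importance is low, because the primary analysis and its decision are unaffected.

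**What to change.** In sections 6 and 6.3.4, replace the agreement rule with a tipping-point analysis:

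- vary the event proportion among missing participants from 0 to 100%, separately in the control and experimental arms;
- keep the two worst-case extremes as corners of that grid;
- report the combinations at which the primary conclusion changes, and discuss how plausible they are.

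Inverse probability weighting stays as planned. The cost is slightly more analysis work and about two sentences of wording. No new data are needed, and the missing-as-failure primary analysis and its decision rule stay as they are. Section 6.3 already allows changes to the analysis plan that are validated before the database is frozen.
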